## Abstract

**Background:**

Improved maternal nutrition and glycaemic control before and during pregnancy are thought to benefit the health of the mother, with consequent benefits for infant body composition and later obesity risk. Maternal insulin resistance and glycaemia around conception and in early pregnancy may be key determinants of maternal physiology and placental function, affecting fetal nutrient supply and maternal-feto-placental communications throughout gestation, with implications for later postnatal health.

**Methods/design:**

This double-blind randomised controlled trial will recruit up to 1800 women, aged 18–38 years, who are planning a pregnancy in the United Kingdom (UK), Singapore and New Zealand, with a view to studying 600 pregnancies. The primary outcome is maternal glucose tolerance at 28 weeks’ gestation following an oral glucose tolerance test. Secondary outcomes include metabolic, molecular and health-related outcomes in the mother and offspring, notably infant body composition. Participants will be randomly allocated to receive a twice-daily control nutritional drink, enriched with standard micronutrients, or a twice-daily intervention nutritional drink enriched with additional micronutrients, myo-inositol and probiotics, both demonstrated previously to assist in maintaining healthy glucose metabolism during pregnancy. Myo-inositol is a nutrient that enhances cellular glucose uptake. The additional micronutrients seek to address deficiencies of some B-group vitamins and vitamin D that are both common during pregnancy and that have been associated with maternal dysglycaemia, epigenetic changes and greater offspring adiposity. Women who conceive within a year of starting the nutritional drinks will be followed through pregnancy and studied with their infants at six time points during the first year of life. Blood, urine/stool, hair and cheek swabs will be collected from the mothers for genetic, epigenetic, hormone, nutrient and metabolite measurements, and assessments of the mother’s body composition, anthropometry, health, diet and lifestyle will be made. Infants will also undergo hair, cheek swab, urine and stool sampling for similar biological measurements; infant body composition will be assessed and feeding recorded.

**Discussion:**

There is an increasing focus on the need to optimise maternal nutrition starting prior to conception. This trial will provide evidence on the potential for nutritional interventions beginning prior to conception to promote healthy maternal and offspring outcomes.

**Trial registration:**

ClinicalTrials.gov, identifier: NCT02509988, Universal Trial Number U1111-1171-8056. Registered on 16 July 2015. This is an academic-led study by the EpiGen Global Research Consortium.

**Electronic supplementary material:**

The online version of this article (doi:10.1186/s13063-017-1875-x) contains supplementary material, which is available to authorized users.

## Background

There is now considerable concern about the maintenance of healthy glucose metabolism during pregnancy. This has arisen by extrapolation from the increasing number of women who develop type-2 diabetes during their reproductive years [1, 2]. Epidemiological studies show that children born to mothers with type-1 or type-2 diabetes also have a greater susceptibility to diabetes and obesity in later life [3, 4]. That this risk is related to intrauterine exposure to hyperglycaemia is shown by the observation that, among siblings, the risk of diabetes is higher in those born after the mother was diagnosed with diabetes [5]. These observations have been extended recently, as offspring exposed to even mild hyperglycaemia during pregnancy have increased adiposity and are at increased risk of later diabetes and cardiometabolic disease [6, 7]. Through transgenerational perpetuation of the cycle of ‘diabetes begetting diabetes’, these factors are driving further escalation of the epidemic of noncommunicable diseases [8, 9].

The rising levels of maternal adiposity and obesity are of particular concern in both developed populations and those undergoing rapid socioeconomic transitions [1, 10, 11]. Maternal obesity is associated with increased risk of short-term adverse pregnancy outcomes as well as longer-term impact on offspring health [12], which have been postulated to be partly mediated by greater maternal insulin resistance and higher glycaemia. Both with and without clinically recognised pregnancy complications, evidence shows that a child of a mother with higher glycaemia per se may suffer from exposure to a suboptimal environment in utero, reducing the likelihood of a healthy body composition in the offspring and predisposing to increased childhood adiposity [13, 14]. Feeding pregnant rodents a high-fat diet gives rise to maternal obesity and hyperglycaemia, and offspring who become overweight demonstrate abnormalities similar to the human metabolic syndrome; these are associated with epigenetic changes such as altered deoxyribonucleic acid (DNA) methylation at specific genetic loci implicated in metabolic functions [15].

Pregnancy represents a state of relative maternal insulin resistance, which helps to promote the transfer of nutrients, such as glucose, fatty acids and amino acids, to the fetus [16]. Placental nutrient transfer is determined by the concentration gradient, blood flow and the operation of active and facilitated transporters [17]. However, in contrast to amino acids, there is no upper limit to placental transfer of glucose and consequent fetal adipose accretion as maternal blood glucose levels rise [13]; this may be viewed as adaptive, as, in the neonatal period, relative adiposity provides metabolic reserves for thermogenesis and critical organs in the event of inadequate maternal care [18]. However, excessive materno-placental glucose transfer is associated with fetal hyperinsulinemia and macrosomia [19, 20] and an increased risk of fatal obstructed labour, suggesting that the levels of glucose exposure of the fetus that are often now experienced are novel in evolutionary terms [21].

Gestational diabetes mellitus (GDM) can be envisaged as the more extreme outcome of physiological processes, when maternal insulin resistance is accentuated by the woman’s own developmental, genetic and environmental circumstances: for example, women who themselves had a lower birth weight [22] or carry genetic variants associated with type-2 diabetes [23, 24] are at increased risk of GDM. Established risk factors for developing GDM include prepregnancy obesity [25], excessive gestational weight gain [26], advanced maternal age [27] and a previous pregnancy with GDM [28]. These factors are now increasingly common in women during their reproductive years with the evolutionary mismatched situation of over-nutrition and low levels of physical activity contributing not only to the rise in GDM but to the increasing prevalence of obesity and diabetes in their children, perpetuating a vicious cycle of disease. Such changes in growth potential and metabolic status may be mediated by inheritable epigenetic alterations occurring in utero [29]. For example, in Canadian first nation peoples, up to 30% of the incidence of type-2 diabetes has its origin in GDM in the previous generation [30]. Higher blood glucose levels in pregnancy carry risk of cardiovascular disease for both the mother as well as the child, a risk which increases with each pregnancy [31].

These findings have significant long-term implications for global public health. Now more than ever, effective strategies for maintaining healthy maternal glucose metabolism in pregnancy are needed. Such strategies would benefit both the mother in terms of a healthy pregnancy and her own metabolic health, and the offspring in terms of promoting healthy body composition and wellbeing.

There are now data indicating that deficiency or low levels of certain micronutrients (vitamins B_6_, B_12_ and D, riboflavin) is extremely prevalent in pregnant women and has lasting effects on the offspring’s risk of obesity, acting through epigenetic processes [32–34]. Evidence from South Asian pregnant women supports a role for the combination of maternal vitamin B_12_ deficiency and folate sufficiency in promoting offspring adiposity, most likely mediated through impaired maternal glucose tolerance during pregnancy [35, 36]. Meta-analysis of observational studies strongly points to a role for maternal vitamin D deficiency in GDM [37], and additional vitamin D in pregnant women with GDM has been shown to have beneficial effects on glycaemia and total and low-density lipoprotein cholesterol (LDL)-cholesterol concentrations [38]. Low zinc intake and status has also been linked with maternal glycaemia [39], and we propose that maternal glucose tolerance may be on the causal pathway linking maternal micronutrient deficiency to offspring adiposity. Importantly, among the pregnant women who we studied in Southampton and Singapore there was a low prevalence of deficiency in folate and iron, the two most common micronutrients currently targeted for supplementation in pregnancy, and neither was associated with altered epigenetic adiposity biomarkers or with the child’s adiposity.

Dietary myo-inositol is found in free form but can also be generated by microbial action in the gastrointestinal tract from food sources of phosphatidylinositol and phytic acid and its salts [40]. Myo-inositol is considered nonessential for mammals because it is synthesised de novo from glucose-6-phosphate in the kidney and other tissues [41, 42]. Abnormalities in its metabolism have been associated with insulin-resistance and its depletion has been frequently observed in tissues affected by diabetic microvascular and neurological complications in animal models and human subjects [43]. Our current understanding of the molecular pathways of insulin action led to the hypothesis that the nutritionally derived myo-inositol may increase insulin sensitivity by making available more phosphatidylinositol and potentially inositol glycan secondary messengers [44, 45]. An increasing number of publications suggest that myo-inositol may reduce insulin resistance during pregnancy [46–49].

Recent studies suggest that specific bacteria may positively influence cardiometabolic parameters, possibly through their interaction with the host and the effect of microbial-derived metabolites. There is now substantial evidence implicating a role for the gut microbiome in affecting glucose metabolism [50], and probiotics may modulate glucose tolerance through balancing gut microbiota, normalising increased intestinal permeability and lowering systemic and local low-grade inflammation [51]. There is preliminary evidence that a combination of probiotic strains during pregnancy may promote the maintenance of healthy glucose metabolism during pregnancy [52].

Taken together, there is strong support for new intervention studies commencing before pregnancy to provide myo-inositol and probiotics, and to improve maternal vitamin B_6_, vitamin B_12_, vitamin D and zinc status, aimed at optimising maternal glycaemia and glucose supply to the feto-placental unit to promote healthy offspring growth and body composition.

## Aim

This double-blind randomised controlled trial in groups of women from different ethnic groups in the UK, Singapore and New Zealand is designed to examine the hypothesis that, compared with standard supplementation, a nutritional drink that contains myo-inositol, probiotics and additional micronutrients, commencing before conception and continuing during pregnancy, will assist in the maintenance of healthy glucose metabolism in the mother and promote offspring health.

## Methods/design

### Trial design

Increasing evidence points to the preconception period and early pregnancy as a critical time when impaired maternal glucose tolerance may lead to biological alterations in the placenta and fetus that result in increased postnatal adiposity in the offspring [53]. As a consequence of this important evidence, our trial uniquely will focus on recruitment before conception and intervention both before and during pregnancy. Substantial experimental evidence from animal studies indicates that preconception is a critical period in the lifecourse for interventions to reduce later risk of metabolic dysregulation in the offspring. In humans, large cohort studies have demonstrated that preconception is a time when factors contributing to later ill-health begin to operate, as poor maternal and paternal diet and smoking before conception impact on development and long-term health of the offspring; to date, however, there are no population-based trials of preconception nutrition in developed communities.

The flow of the trial is shown in the Standard Protocol Items: Recommendations for Interventional Trials (SPIRIT) Figure (Fig. 1). See Additional file 1 for the SPIRIT checklist. Extensive biosampling and detailed phenotyping are embedded in the study with longitudinal assessments at multiple time points starting from the preconception phase throughout pregnancy and into the first year post delivery. The biosampling and phenotyping will enable detailed mechanistic insights and characterisation of potential new interventions for investigation in future studies. Following informed consent at the first preconception visit, a baseline standard 75-g oral glucose tolerance test (OGTT) will be conducted, nutritional status, lifestyle, mood, body anthropometry and metabolic phenotype ascertained and biosampling undertaken, followed by randomisation to the intervention or control drink. At the second preconception visit a month later, further biosampling will be undertaken and body composition assessed by DXA (dual-energy X-ray absorptiometry) scanning. Regular in-person and phone contact will be made with participants to resupply control/intervention drinks, and to encourage retention and compliance during the preconception phase. Participants who become pregnant within a year of commencing the intervention or control drink will be seen around 7, 12, 20, 28 and 34 weeks of pregnancy for further phenotyping, biosampling and ultrasound scans assessing fetal growth and development. At 28 weeks’ gestation, a standard 75-g OGTT will be repeated to ascertain the primary outcome. Normal antenatal care will be permitted during the trial. The fathers will be interviewed to ascertain paternal lifestyle and mood, their anthropometry measured and paternal biosamples collected. At birth, offspring cord blood, umbilical cord and placental samples will be collected. Neonatal body composition is assessed by anthropometry, air displacement plethysmography (PEA POD) and, in a subsample, by DXA scanning. Both breast- and formula-fed infants will be followed up when the infant is aged 1, 3 and 6 weeks, and 3, 6 and 12 months; infant feeding will be assessed in detail, biosamples collected and growth and wellbeing ascertained. Breast milk samples will be collected from a subset of participants in early infancy for nutrient and metabolic analysis. A maternal OGTT will be repeated again at 6 months postpartum and repeat biosamples collected. The site visits will be completed at the research and hospital facilities of the three sites in Auckland (University of Auckland, Auckland, Waitemata and Counties Manukau District Health Boards and Clinics, New Zealand), Singapore (National University Hospital and National University Health System Investigational Medicine Unit) and Southampton (National Institute for Health Research Wellcome Trust Southampton Clinical Research Facility and Princess Anne Hospital, University Hospital Southampton, UK).

**Fig. 1 Fig1:**
[figure not shown]
Standard Protocol Items: Recommendations for Interventional Trials (SPIRIT) Figure: trial schema. Abbreviations: *PCV* preconception visit, *PC* preconception, *PGV* pregnancy visit, *PDV* post-delivery visit, *BIA* bioelectrical impedance analysis, *BP* blood pressure, *DM* diabetes mellitus, *DXA* dual-energy X-ray absorptiometry, *GDM* gestational diabetes, *HIV*, human immunodeficiency virus, *IFG* impaired fasting glucose, *IGT* impaired glucose tolerance, *NGT* normal glucose tolerance, *OGTT* oral glucose tolerance test, *USS,* ultrasound scan. Questionnaires: *BEBQ* baby eating behaviour, *BM* breast milk, *FH* family history, *GH* general health, *IFH* infant feeding and health, *IIF* intentions for infant feeding, *L* lifestyle, *M* mood (Edinburgh Postnatal Depression Scale, State-Trait Anxiety Inventory), *MH* medical history, *MSH* menstrual history, *MTH* maternal health, *N* nutrition/diet, *OH* obstetric history, *PA* physical activity, *S* sleep. Biosampling: # = blood, ♥ = breast milk, $ = buccal swabs, * = epithelial swabs, @ = hair, ^ = stool, ~ = urine

### Recruitment

Recruitment will be via self-referral of interested women who hear about the study via one or more of the following: (1) local site advertisements in social (e.g. Facebook) and general (e.g. radio, local newspapers, magazines, posters) media, (2) information brochures given to women engaging in community groups such as religious, culture-based or special-interest groups, (3) information brochures given to women identified through or attending primary medical care, family planning or hospital clinics (for this group, eligible women may be contacted by a research nurse if they give permission to the clinic to pass on their contact details for this purpose).

Inclusion criteria are women who meet the following:Aged 18–38 yearsLiving in Southampton, Singapore or AucklandIn Southampton and Auckland, planning to have future maternity care in Southampton and Auckland, respectivelyIn Singapore, willing to deliver at the National University HospitalWomen planning to conceive within 6 months (but conception up to 12 months after phenotyping will still be included)In Singapore only women of Chinese, Malay and Indian ethnicity, or of mixed Chinese/Malay/Indian ethnicity will be includedAble to provide written, informed consent

Exclusion criteria are:Pregnant or lactating at recruitment (women who are currently breastfeeding will be excluded, but no washout period from the end of breastfeeding will be required before study start)Assisted fertility apart from those taking clomiphene or letrozole aloneWomen with pre-existing type-1 or type-2 diabetes (fasting plasma glucose concentration ≥7.0 mmol/L or post OGTT 2-h plasma glucose concentration ≥11.1 mmol/L)Oral or implanted contraception currently or in the last month, or with an intrauterine contraceptive device in situMetformin or systemic steroids currently or in the last monthAnticonvulsant medication currently or in the last monthTreatment for HIV, Hepatitis B or C currently or in the last monthKnown serious food allergy

Withdrawal criteria are:The participant wishes to discontinue participation in the studyThe participant is unwilling or unable to comply with the protocol (including attendance at study visits, having study measures and biosampling)An overall uptake level of intervention/control nutritional drink of less than 60% evidenced by sachet countingThe participant is pregnant before or at preconception visit 2The participant suffers a miscarriage (pregnancy loss before 24 weeks’ gestation) or ectopic pregnancy. If the participant suffers a first-trimester pregnancy loss and wishes to re-join the study, she will be re-characterised as at the first baseline visit a month or more after a negative pregnancy test and will be assigned the nutritional drink with the same randomisation code as beforeThe participant presents with a multiple pregnancy (twins or other multiples)The infant dies in the perinatal period (for post-birth secondary outcomes)The participant suffers an adverse reaction which is deemed by the investigator to be causally related to the interventionThe participant is withdrawn at the discretion of the investigator for medical reasons

For participants who withdraw during the pregnancy phase of the study, consent will be obtained to follow up on key outcome measures from their medical records to enable comparison of the characteristics of withdrawn and studied participants.

### Randomisation procedure

At preconception clinic visit 1 all eligible participants will be randomised via the electronic study database to either the nutritional drink or the control drink. This database will assign each participant the appropriate code number that is consistent with either the intervention nutritional drink arm or the control drink arm. Randomisation will be stratified by site to ensure balanced allocation of participants across the two arms at each of the three sites, with further stratification by ethnicity. Investigational products will be blinded by the manufacturer with nonspeaking codes that do not allow deduction of the identity of intervention or control drinks. Investigators, staff performing the assessments and data analysts will remain blind to the identity of the allocation from the time of randomisation until either the participant is unblinded or database lock of the primary outcome occurs. If emergency unblinding is necessary, the process for this will be documented in the study Safety Monitoring Plan.

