### Trial status

Recruitment for the trial commenced on 3 August 2015; more than half of the participants have been recruited within the following 12 months and recruitment remains ongoing in October 2016. Participants have already progressed through the randomisation and pregnancy phases of the study and initial deliveries have occurred in all three sites.

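### The blinding commitment for assessors ends at lock of the 28-week primary outcome, leaving later infant assessments, chiefly the 12-month visits, without protection

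*Protocol article*

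**What the plan says.** The Randomisation procedure section sets both the scope and the end of blinding: "Investigators, staff performing the assessments and data analysts will remain blind to the identity of the allocation", and this holds "from the time of randomisation until either the participant is unblinded or database lock of the primary outcome occurs". The section also provides for emergency unblinding under the Safety Monitoring Plan.

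The Trial design section places the primary outcome at 28 weeks' gestation, when "a standard 75-g OGTT will be repeated to ascertain the primary outcome". Data collection continues well beyond that. Infants are seen "when the infant is aged 1, 3 and 6 weeks, and 3, 6 and 12 months", with feeding, growth, wellbeing and biosamples recorded. On the mother's side, "A maternal OGTT will be repeated again at 6 months postpartum".

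Under Outcome measurements, the secondary offspring outcomes include adiposity gain over infancy (analysed with regard to feeding) and offspring wellbeing and cardiometabolic risk factors, including visceral adiposity. The Abstract singles out infant body composition among the secondary outcomes.

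The article gives no date for the primary lock. It does not say that the lock waits for infant follow-up, and it does not say who receives allocation codes when the lock occurs.

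**The concern.** The end of blinding is tied to a milestone that suits the primary outcome but not the outcomes collected after it. Once the primary data are locked, the article no longer obliges the people who measure infants, interview mothers about feeding and record wellbeing to remain blind.

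These measurements depend partly on the observer. An assessor who knows the allocation can influence positioning, repeat readings, probing of answers and the effort put into retaining a family. Feeding data matter twice, because they also enter the analysis of adiposity gain. Exposure would follow calendar time, so families recruited late would be assessed under different conditions from those recruited early. Data analysts are released at the same point, before the infant outcomes are complete.

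At stake is the credibility of the infant secondary outcomes in a trial described as double-blind. Blinding that has been lost cannot be restored.

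**Working it through.** The plan has no figure of its own to reproduce here. Two quantities were checked: the length of the unprotected interval, and the share of visits that could fall in it.

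**1. Length of the interval**

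Formula: (gestation at birth − 28 weeks) ÷ 4.345 weeks per month, plus the infant's age at the visit. The 28-week and 12-month points come from the Trial design section. Gestation at birth is an assumption.

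- Birth at 37 weeks: 9 ÷ 4.345 = 2.07; to the 12-month visit, 14.1 months.
- Birth at 40 weeks: 12 ÷ 4.345 = 2.76; to the 12-month visit, 14.8 months.
- Birth at 42 weeks: 14 ÷ 4.345 = 3.22; to the 12-month visit, 15.2 months.

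To the 6-month visit the interval is 8.1 to 9.2 months. About 15 months is thus an upper bound: it applies to the last participant, with a lock straight after her OGTT.

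**2. Share of visits after the lock**

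This depends on how the 28-week OGTTs are spread over calendar time and on the lock date, which is not stated. A simulation of 600 pregnancies (100 runs per setting) used these inputs:

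- *Recruitment:* uniform over 15 to 24 months (assumed). The Trial status section reports a start on 3 August 2015 and that "more than half of the participants have been recruited within the following 12 months and recruitment remains ongoing in October 2016". Recruitment open in October 2016 implies at least 14 months; more than half in 12 months, at a uniform rate, implies less than 24.
- *Conception:* monthly chance of 10-20% (assumed), from 1 to 12 months after starting the drink. The upper limit follows the Trial design section, which follows up "Participants who become pregnant within a year of commencing the intervention or control drink". The lower limit reflects withdrawal of women pregnant by the second preconception visit, a month after the first.
- *Birth:* 40 weeks (assumed).
- *Lock:* 0, 3, 6, 12 or 15 months after the last 28-week OGTT (assumed).

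A visit counts as exposed if (OGTT date + 12 weeks + infant age at visit) is later than the lock date. Ranges across the recruitment and conception settings:

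| Lag from last OGTT to lock | Birth measures | 3-month visit | 6-month visit | 12-month visit |
|---|---|---|---|---|
| 0 months | 1-2% | 4-9% | 12-21% | 37-61% |
| 3 months | 0% | 1-2% | 5-9% | 24-40% |
| 6 months | 0% | 0% | 1-3% | 12-22% |
| 12 months | 0% | 0% | 0% | 1-2% |
| 15 months | 0% | 0% | 0% | 0% |

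**3. Cross-check**

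If OGTTs accrued evenly over 24 to 36 months, the share of 12-month visits after an immediate lock would be 14.8 ÷ 36 = 41% to 14.8 ÷ 24 = 62%, close to the simulated range. For the 6-month visit the same shortcut gives 8.8 ÷ 36 = 24% to 8.8 ÷ 24 = 37%. That is too high, because variable time to conception leaves only a thin tail of late OGTTs. The simulated 12-21% is the better guide.

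**The case against.** **Would the later outcomes actually be measured by unblinded staff?** A reader might infer this, but the article does not support it. The rule says how long blinding is guaranteed. It does not say that sites receive individual codes at lock, and a late lock would leave few or no visits exposed. What the text supports is that such assessments *may* be made by staff no longer required to be blind.

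**Are all postnatal outcomes affected?** No.

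- Neonatal PEA POD adiposity is almost untouched, at 1-2% even with an immediate lock.
- Birthweight and cord C-peptide are fixed at birth.
- The 6-month maternal OGTT yields a laboratory value and is not among the listed secondary outcomes.
- Metabolomic, epigenetic and microbiota outcomes are laboratory assays.
- Skinfolds are not named as a trial measurement; they appear only where the HAPO study is described.
- The rule does not release participants, so it does not itself bias what mothers report.
- The drinks are described as taken before and during pregnancy, so there is little scope for performance bias during infancy.

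All of this stands and narrows the point.

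**Is this detail left to a fuller document?** An article need not describe code custody or an analyst firewall, and the Statistical analysis section says the analysis plan is finalised before unblinding. That does not dispose of the point. The article is not silent here: it states an end to blinding and names assessment staff within it. If a fuller document is stricter, this sentence conflicts with it and still needs correcting.

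**Conclusion.** The concern holds in a limited form. The stated commitment for assessors stops at lock of the 28-week outcome, and nothing in the article carries it through to the end of infant follow-up.

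The exposure is mainly at the 12-month visit, and its size turns on the unstated lock date. If the 500 live births anticipated under Power calculations all attended at 12 months, the immediate-lock range corresponds to 0.37 × 500 = 185 to 0.61 × 500 = 305 infants. With a 6-month lag it is 0.12 × 500 = 60 to 0.22 × 500 = 110, and with a 15-month lag none. These figures rest on the assumed recruitment, conception and lock timings; only the interval of about 15 months follows from the visit schedule almost directly.

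The consequence is a risk of detection bias in infant adiposity gain, anthropometry, and feeding and wellbeing data collected by staff. The primary outcome is not affected. The defect is worth correcting because it cannot be repaired after the lock and the correction is cheap.

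**What to change.** Amend the blinding sentence in the Randomisation procedure section so that:

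- site investigators and all outcome assessors stay blind until the 12-month infant data are complete and locked;
- at primary lock, allocation is released only to a separate analysis team with no role in data collection;
- primary results are reported at group level, with no individual codes passed to sites before the infant data are locked;
- the existing emergency unblinding exception is kept.

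Under this rule no scheduled infant visit falls after the end of assessor blinding. The cost is a change of wording, a firewall around the analysis team, and a later date at which sites learn allocations. It should be in place before the primary lock.
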